### Sample size calculation

The sample size calculation is based on the primary endpoint change in the bowel-score according to EORTC QLQ-PR25 from baseline to 12 weeks. Based on numerous trials, we assume a change of 6.5 points in the standard arm (arm 1). Based on the two phase II trials mentioned above, we assume a change of 6.5 points in arm 2 as well and a change of 2.5 points in arm 3. Equal standard deviation of 15 points is expected for all arms. In the primary analysis, arm 1 will be compared with arm 3 and arm 2 with arm 3. To control the overall type I error of 5%, local significance levels of 2.5% according to Bonferroni were applied in the sample size calculation. To achieve a power of 80% with the assumptions above, a sample size of 269 per arm results for the two-sided t-test. Calculations have been performed using PASS 14.0.8. The primary analysis will be performed applying the Bonferroni Holm procedure and the factors used in the stratified randomization will be considered. This will lead to an increase in power. Based on the experiences from previous studies, a conservative rate of drop-outs and loss to follow-ups of 10% is expected. To compensate for this loss in information, 299 patients per arm are required resulting in a total of 897 patients to be randomized.

### Statistical analysis

In the primary analysis, arm 1 vs. arm 3 and arm 2 vs. arm 3 will be compared regarding the primary endpoint applying a linear regression model including the stratification variables used in the randomisation procedure and center. Primarily, the analysis will be based on the Intention to treat population which consists of all randomized patients treated at least for 1 week in the arm as randomized. Missing values for the primary endpoint will be imputed using multiple imputations under the “missing at random” assumption and the results will be pooled. To control the global type I error rate with 5%, the Bonferroni Holm procedure will be applied. In case that at least one of the two comparisons can be considered significant, arm 1 vs. 2 will be compared at a significance level of 5%, still controlling the global significance level of 5%.

In addition, a complete case analysis will be carried out. In the per protocol set only patients who were treated as described in the protocol with complete documentation of relevant data will be considered. This set will be analyzed as well as sensitivity analysis.

Time to event endpoints will be analyzed using Cox proportional hazard models adjusting for the stratification variables used in the randomization procedure. All secondary endpoints will be descriptively analyzed using statistical methods as appropriate for the underlying distribution of the data.

Safety endpoints will be analyzed based on the safety population which comprises all patients who had at least 1 day of treatment, considered in the arm as treated. Rates of acute and chronic toxicity will be calculated together with corresponding 95 confidence intervals for group comparisons. Descriptive *p*-values for the chi-squared test will be provided. Statistical methods will be used to assess the quality of the data, homogeneity of treatment groups, endpoints and safety of the two intervention groups. Details of the statistical analysis will be fixed at the latest in the Statistical Analysis Plan (SAP) to be prepared before database closure. This also includes the definition of the analysis populations.

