## Methods

### Primary and secondary endpoints

The primary endpoint is defined as the change in the bowel-score according to EORTC QLQ-PR25 from baseline to 12 weeks after start of proton therapy compared to photon irradiation.

Secondary endpoints are bPFS after 5 years, quality of life (QoL) according to EORTC QLQ-C30 and –PR25 after 2 and 5 years, clinical symptoms and toxicity according to National Cancer Institute Common Terminology Criteria for Adverse Effects (NCI CTCAE) version 5.0 after 2 and 5 years as well as overall survival (OS) after 5 years.

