### Pretreatment preparations/ randomization

When meeting the inclusion criteria, patients are informed about the trial including potential risks and benefits. After written informed consent, patients will be allocated (1:1:1) in concealed fashion into one of the three treatment arms (arms 1–3). Block randomization will be carried out with permuted block sizes and stratified by Gleason Score (GS) (≤ 7 vs. > 7) and treatment indication (adjuvant vs. salvage) using a centralized web-based tool (www.randomizer.at). Participating sites have to register at the randomization platform before. All required documentation will be transferred to the study center (Study Administration, Department of Radiation Oncology, Heidelberg University Hospital, [name]).

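### The primary model for change in bowel score does not name the baseline score as a covariate: the analysis is valid, but it may give up precision

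*Protocol article*

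**What the plan says.** The protocol article (Primary and secondary endpoints) defines the primary endpoint as the "change in the bowel-score according to EORTC QLQ-PR25 from baseline to 12 weeks after start of proton therapy", compared with photon irradiation. Under Statistical analysis, arm 1 vs arm 3 and arm 2 vs arm 3 are compared with a "linear regression model including the stratification variables used in the randomisation procedure and center". The randomization section gives the stratification variables as Gleason Score in two groups and adjuvant or salvage indication.

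The Sample size calculation section takes the same line: "The primary analysis will be performed applying the Bonferroni Holm procedure and the factors used in the stratified randomization will be considered". It adds that this will raise the power. The baseline bowel score is not named as a covariate or as a stratification factor anywhere in the article. Further analysis details are left to a statistical analysis plan due before database closure, which is not shown.

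**The concern.** Subtracting the baseline value from the week-12 value is the same as fitting the baseline with a slope of exactly 1. A regression that includes the baseline estimates that slope from the data. In large samples the estimated slope never gives a less precise treatment contrast than the fixed one. It gives a more precise contrast whenever the true slope differs from 1.

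The article does look to covariates for extra power, but the ones it names are two oncological factors and centre. The baseline value of the outcome, which a change score needs in any case, is not among them. At stake is the precision of both confirmatory comparisons, and how far a chance difference in baseline bowel score between arms carries over into the estimated effect.

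**Working it through.** **Inputs from the Sample size calculation section.** For the photon hypofractionation and proton arms: "we assume a change of 6.5 points in arm 2 as well and a change of 2.5 points in arm 3". Arm 1 is also set at 6.5 points, so each comparison has a difference of 6.5 − 2.5 = 4 points. "Equal standard deviation of 15 points is expected for all arms". For alpha, "local significance levels of 2.5% according to Bonferroni were applied in the sample size calculation". Power is 80%, the test is a two-sided t-test, and dropout is 10%.

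**Inputs not in the documents (assumed).** rho, the correlation between baseline and week-12 score, and k = baseline SD / week-12 SD. Both are varied below.

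**1. Reproduce the stated sample size.** The normal approximation gives n = 2 × (15/4)² × (2.241 + 0.842)² = 28.125 × 9.505 ≈ 267.3, so 268 per arm. The exact noncentral t calculation gives power 0.7990 at 268 and 0.8007 at 269, so 269 per arm. Allowing for dropout, 269 / 0.9 = 298.9, so 299 per arm, and 3 × 299 = 897. The stated figures are correct for an unadjusted t-test on change.

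**2. Variance with and without baseline in the model.** Take the week-12 SD as the unit.
- Variance of the change score: 1 + k² − 2·rho·k
- Residual variance with baseline fitted: 1 − rho²
- Ratio R = (1 − rho²) / (1 + k² − 2·rho·k) = 1 − (k − rho)² / (1 + k² − 2·rho·k)

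R is never above 1. With k = 1 it reduces to (1 + rho)/2. With rho = k it equals 1, so there is no gain.

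**3. Power at 269 per arm.** Replace the SD of 15 by 15·√R in the same two-sided t-test at 2.5% with a difference of 4 points. Without adjustment the power is 80.1%.

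| k | rho = 0.3 | rho = 0.5 | rho = 0.7 |
|---|---|---|---|
| 1.0 | R 0.650, 94.4% | R 0.750, 90.7% | R 0.850, 86.5% |
| 0.8 | R 0.784, 89.3% | R 0.893, 84.7% | R 0.981, 80.9% |
| 0.6 | R 0.910, 84.0% | R 0.987, 80.6% | R 0.981, 80.9% |

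With k = 1 and rho = 0.9, R is 0.95 and power is 82.2%.

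**4. What remains of a chance baseline imbalance.** Given a baseline difference D between two arms, the change-score contrast shifts by (rho/k − 1)·D. With k = 1 the size of this shift is (1 − rho)·D. An SD of change of 15 then implies a score SD of 15 / √(2(1 − rho)), and the standard error of D is that SD × √(2/269).

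| rho (k = 1) | Score SD | SE of D | Shift for a one-SE imbalance |
|---|---|---|---|
| 0.3 | 12.68 | 1.09 | 0.77 points |
| 0.5 | 15.00 | 1.29 | 0.65 points |
| 0.7 | 19.36 | 1.67 | 0.50 points |

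At rho = 0.5 the shift is 0.65 / 4, about 16% of the difference the trial is sized to detect.

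**The case against.** The strongest reply is that nothing here is wrong. Endpoint, sample size and model agree with each other, the change-score contrast is unbiased under randomization, and the planned 80% power is kept. That stands, and it limits the point to an improvement on a valid analysis.

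A second reply is that the covariate list is open (the model is one that includes these terms) and that the analysis plan may add the baseline score. This also stands in part: a reader should not infer that the article rules out baseline adjustment. But the article is not silent on covariates. It names them, down to centre, in the section on the primary analysis. The arms differ visibly (35 against 19 fractions), so a covariate added late to a published primary model would be harder to defend than one named now.

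A third reply concerns size. The 94, 91 and 87% figures belong to equal SDs at both times, which is the favourable row. The article expects scores to change by 6.5 points under photons, so a wider spread at week 12 than at baseline is plausible, and the gain can then be under one percentage point. This stands fully.

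Some stronger readings are tempting but not supported:
- **That baseline imbalance is left uncorrected.** The change score removes it with slope 1; only the part in step 4 remains.
- **That baseline is the most prognostic covariate, or must correlate negatively with change.** The documents hold no data on either. The second needs rho below k; at rho = 0.7 and k = 0.6 the sign is reversed.
- **That the trial is too small.** The stated numbers reproduce.
- **That every patient has a baseline score.** The visit schedule is not shown, and imputation of missing endpoint values is planned.

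**Conclusion.** The point holds as a recommended improvement, not as an error. The named covariates leave out the baseline bowel score, and the implied fixed slope of 1 cannot be more efficient in large samples than an estimated one.

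The direction is secure; the size is not. In the scenarios computed, power per comparison would move from 80% to somewhere between about 81% and 94%, and there is no gain at all when rho equals k. The calculation assumes the article's difference of 4 points and SD of 15, 269 evaluable patients per arm, a common linear baseline slope, and no contribution from the other covariates. The statement that the planned analysis is valid concerns the choice of covariates; the definition of the analysis population is a separate matter.

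**What to change.** State in the protocol or the analysis plan, before any outcome data by arm are seen, that the primary linear model contains the baseline QLQ-PR25 bowel score as a linear covariate, next to the stratification variables and centre. Use the same covariate in the complete-case and per-protocol models, and make sure that the multiple-imputation model contains it; the article does not list that model's variables, so it may already be there.

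Without a treatment-by-baseline interaction, the treatment coefficient remains a difference in mean change. It is the same whether the outcome is entered as change or as the week-12 score.

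The cost is a sentence of text and one degree of freedom. No new data are needed, because the endpoint already requires the baseline score. The sample size of 897 should stay: since the gain may be close to zero, it is no basis for a reduction.

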### Irradiation

Treatment planning and application will be performed at the site of study enrollment. For centers without a proton unit, patients randomized in arm 3 will be referred to one participating site with protons available. Patient positioning and immobilization will be performed according to institutional standards. Photon irradiation will be applied in IMRT/ image-guided radiotherapy (IGRT) technique, proton beam therapy is performed as active beam application (raster scanning method).

For contouring, the bladder, rectum, posterior third of the rectum, bowel (small bowel, colon/ sigma) and femoral heads will be defined as organs-at-risk (OAR). Target volume delineation will be done according to Radiation Therapy Oncology Group (RTOG) guidelines (post-OP prostate cancer). The planning target volume (PTV) will be obtained by adding a 5 mm (anterior-posterior; superior-inferior) and 7 mm (lateral direction) margin to the clinical target volume (CTV), respectively. Total dose will be prescribed to 50% of the PTV for each treatment arm. Equivalent dose in 2.0 Gy/ fraction (ED2) for hRT (arm 2 + 3) is 69.7 Gy, calculated for 2.0 Gy single dose considering an α/β value of 2.5. For proton irradiation, dose will be calculated with an RBE of 1.1 according to ICRU 78.

Dose to OAR may not exceed the tolerance dose (TD) 5/5 (toxic dose leading to 5% severe complications over 5 years). The maximum dose of PTV_rectum (defined as the intersection between PTV and the rectum) is 70.0 Gy (arm 1) and 57.0 Gy (RBE) (arm 2 + 3), respectively. In the hRT arm, maximal EQD2 for the rectum is 66.5 Gy (RBE) (α/β value of 4).

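### The primary population labelled intention to treat is restricted by treatment received after randomisation, and no analysis of all randomised patients is stated

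*Protocol article*

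**What the plan says.** The Statistical analysis section of the Protocol article names the population for the primary analysis: "Intention to treat population which consists of all randomized patients treated at least for 1 week in the arm as randomized". Missing primary-endpoint values are to be multiply imputed under missing at random. A complete case analysis and a per protocol analysis are added, and safety is analysed by treatment received. The section leaves details to a later SAP and adds: "This also includes the definition of the analysis populations".

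Under Pretreatment preparations/ randomization, "patients will be allocated (1:1:1) in concealed fashion into one of the three treatment arms". Under Irradiation, the default is that "Treatment planning and application will be performed at the site of study enrollment"; but where the centre has no proton unit, "patients randomized in arm 3 will be referred to one participating site with protons available".

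Under Sample size calculation: "In the primary analysis, arm 1 will be compared with arm 3 and arm 2 with arm 3".

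**The concern.** An intention-to-treat set is fixed at randomisation. This one is fixed later, by three facts: whether treatment began, whether it lasted a week, and whether it was the allocated treatment. Taken at its word, the definition removes a patient allocated to protons but treated with photons instead of analysing that patient in arm 3.

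No other stated analysis repairs this. Imputation fills gaps only for patients already in the set. The complete case and per protocol analyses are no wider. The safety set follows treatment received.

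The design gives a reason to expect uneven exclusion. The referral step comes after allocation and exists only in arm 3, for patients from centres without a proton unit. Both primary contrasts run through arm 3, so a distortion there would reach both. At stake is whether the main result of a phase III trial can be reported as an intention-to-treat result.

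**Working it through.** **1. The plan's own sample size.** Inputs from Sample size calculation: change of 6.5 points in arms 1 and 2, 2.5 points in arm 3, SD 15, two-sided 2.5% per comparison, power 80%, loss 10%.

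- Target difference: 6.5 − 2.5 = 4.0 points.
- Normal approximation: n = 2 × 15² × (2.241 + 0.842)² / 4² ≈ 267.3, so 268 per arm. The exact t-test calculation gives 269 (power 80.1%).
- 269 / 0.9 = 298.9, so 299 per arm; 3 × 299 = 897.

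The stated figures reproduce. The problem is the population, not the arithmetic.

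**2. Who is in which set.**

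| Patient | Primary set, read literally | All randomised, as allocated |
|---|---|---|
| Never starts treatment | out | in |
| Stops within the first week | out | in |
| Treated in another arm | out | in, allocated arm |
| Treated at least 1 week as allocated | in | in |

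**3. How large the bias could be.** Let x be the share excluded from arm 3 only, and g the difference in mean change between excluded and retained arm 3 patients. Then bias = x × g. Neither x nor g is in the article; both are assumed here. The standard error of a contrast is 15 × √(2/269) = 1.29 points. The last column is the chance of a significant result in a single comparison, in either direction, when the true difference is zero (269 per arm, nominal 2.5%).

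| x (patients of 299) | g | Bias | Share of 4 points | Per-comparison error |
|---|---|---|---|---|
| 2% (6) | 5 | 0.10 | 2.5% | 2.5% |
| 5% (15) | 5 | 0.25 | 6.2% | 2.8% |
| 5% (15) | 10 | 0.50 | 12.5% | 3.6% |
| 10% (30) | 10 | 1.00 | 25% | 7.2% |

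**4. What the correction costs in power.** If a share x of arm 3 receives photons and has the photon change of 6.5, the difference as allocated is 4 × (1 − x).

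| x | Difference | Power, 269 informative per arm | Power, 299 informative per arm |
|---|---|---|---|
| 0% | 4.0 | 80.1% | 84.4% |
| 5% | 3.8 | 75.5% | 80.2% |
| 10% | 3.6 | 70.4% | 75.4% |

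**The case against.** The case on the other side has several parts.

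- **The wording may be loose.** The safety sentence in the same section sets a minimum treatment time and then says how patients are assigned to arms. Read in parallel, the primary definition could mean treated for a week and analysed as randomised, which keeps crossovers. That is possible, though the literal text says otherwise. Even so, never-starters and first-week stoppers are still dropped, so the point survives in reduced form.
- **There is a practical reason for the restriction.** The sections on endpoints and follow-up count the 12 weeks from the start of treatment, so a never-treated patient has no defined week 12. Imputation given allocated arm alone would also tend to hand untreated arm 3 patients proton-like values. Both objections stand, and the correction has to deal with them.
- **The model adjusts for centre.** This partly absorbs differences between centres with and without protons. Selection within a centre remains.
- **The gap may be small.** The upper assumed gaps of 5 to 10 points exceed the whole 4-point target. If patients drop out mainly because of travel, the gap could be near zero. Exclusions in arms 1 and 2 could also offset those in arm 3.
- **Populations are left to the SAP.** Deferring further detail is ordinary practice and not a separate defect. It does not cure a definition already written down, but it leaves room to correct it.

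A reader might infer that the comparison is biased in favour of protons, or that exclusions do concentrate in arm 3. The article supports neither. It reports no non-start, early-stop or crossover rate by arm, and nothing fixes the sign of the gap. Concentration in arm 3 is an inference from the referral rule.

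**Conclusion.** The point holds. The primary population carries the wrong label, excludes patients on post-randomisation grounds, and is not backed by any stated analysis of all randomised patients as allocated. Comparability by randomisation is no longer guaranteed, which is not to say that it has been lost.

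The size is unknown. Under exclusion from arm 3 only, the assumed inputs span a bias that can be ignored (2% excluded, 5-point gap) to one that matters (10% excluded, 10-point gap, error nearly three times nominal). These figures are illustrations and not estimates for this trial. The definition needs correcting because it governs the confirmatory result, and because questionnaires not sought from untreated or switched patients may not be recoverable later.

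**What to change.** - Define the primary population as all randomised patients, analysed in the allocated arm whatever treatment was started or received.
- Seek the 12-week questionnaire from every randomised patient, and state the time origin for those never treated, for example randomisation or planned start.
- Apply the planned multiple imputation to this set, with treatment actually received taken into account.
- Keep the one-week set as a sensitivity analysis under the name modified intention to treat, say explicitly whether crossovers belong to it, and report exclusions by arm with reasons.

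The cost is wording, some additional questionnaires, and dilution if patients cross over. The planned 10% allowance covers lost information and not dilution. With 269 informative patients per arm, power would be about 75.5% at 5% and 70% at 10% crossover from protons to photons. This should be disclosed; the correction does not require a larger sample.

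### Toxicity is compared with an unstratified chi-squared test although randomisation is stratified; a stratified comparison would be a free, low-severity improvement

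*Protocol article*

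**What the plan says.** Under Pretreatment preparations/ randomization, "patients will be allocated (1:1:1) in concealed fashion into one of the three treatment arms", using permuted blocks "stratified by Gleason Score (GS) (≤ 7 vs. > 7) and treatment indication (adjuvant vs. salvage"). Two binary factors give four strata.

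The Statistical analysis section carries these factors into two analyses. The linear model for the bowel score includes them together with center. For survival-type endpoints, "Time to event endpoints will be analyzed using Cox proportional hazard models adjusting for the stratification variables used in the randomization procedure".

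Toxicity is handled differently: "Rates of acute and chronic toxicity will be calculated together with corresponding 95 confidence intervals for group comparisons". Then: "Descriptive *p*-values for the chi-squared test will be provided". Neither sentence mentions the strata, and the method for the intervals is not named. The analysis set is the safety population, with patients counted in the arm whose treatment they received. More generally, "All secondary endpoints will be descriptively analyzed using statistical methods as appropriate for the underlying distribution of the data".

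The Abstract lists toxicity among the secondary aims on which hypofractionated treatment is to be shown non-inferior to normofractionated treatment. Toxicity is therefore a comparative aim, not only a safety listing.

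**The concern.** Blocking within strata keeps the arms close to balanced on Gleason score and indication. The part of the chance difference between arms that would come from unequal strata is largely removed by design. An unstratified variance still counts that part. If the strata are prognostic for toxicity, the standard error is then larger than the design warrants, the p-value too large and the interval too wide.

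The direction matters for this aim. A non-inferiority reading rests on an interval bound, and an unnecessarily wide interval makes it harder to support. For a safety signal, a conservative comparison makes real harm slightly harder to see. How far this matters depends on how strongly the strata predict toxicity.

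**Working it through.** **Figures in the article.** The article gives no figure for the toxicity comparison. Its only sample size is for the bowel score, and it reproduces: a difference of 6.5 − 2.5 = 4 points, SD 15, two-sided 2.5% and 80% power give 268.6 per arm with the t-test, so 269; 269 / 0.90 = 298.9, so 299; 3 × 299 = 897. It does not depend on the toxicity test.

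**Formula.** Take two arms of equal size, balanced across equally large strata with toxicity rates p_s and mean rate p. The true variance of the difference in rates is proportional to W = mean of p_s(1 − p_s). The unstratified analysis uses T = p(1 − p). With R = W/T:

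- true size of the nominal 5% test ≈ 2 × [1 − Φ(1.96/√R)]
- excess interval width = 1/√R − 1

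1 − R equals the variance of the stratum rates divided by p(1 − p), so the absolute spread of the rates drives the effect. If the rates are equal, R = 1 and nothing is lost.

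**Inputs.** 1:1:1 allocation and four strata come from the article. The toxicity rates by stratum, the equal strata and the exact balance are assumptions.

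**One case in full.** Rates 10/20/20/30%: W = (0.09 + 0.16 + 0.16 + 0.21)/4 = 0.155; T = 0.20 × 0.80 = 0.16; R = 0.969. Size ≈ 2 × [1 − Φ(1.99)] = 4.6%. Excess width = 1/√0.969 − 1 = 1.6%.

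**Four strata, 300 per arm, 200,000 simulations.** The stratified test is Cochran-Mantel-Haenszel (CMH).

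| Stratum rates (%) | R | Size, chi-squared | Size, CMH | Excess width | Power for +10 points, chi-squared → CMH |
|---|---|---|---|---|---|
| 20 in all | 1.00 | 5.0% | 5.0% | 0 | 81.1 → 81.1% |
| 15/20/20/25 | 0.992 | 4.9% | 5.0% | 0.4% | 81.3 → 81.4% |
| 10/20/20/30 | 0.969 | 4.6% | 5.0% | 1.6% | 81.3 → 82.1% |
| 10/25/25/40 | 0.940 | 4.3% | 5.0% | 3.1% | 77.1 → 78.9% |
| 10/10/40/40 | 0.880 | 3.7% | 5.0% | 6.6% | 77.6 → 81.0% |
| 5/20/20/50 | 0.853 | 3.4% | 5.0% | 8.3% | 79.0 → 83.0% |
| 1/2/2/4 (rare) | 0.995 | 5.0% | 4.8% | 0.3% | not informative |

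In the two modest cases (second and third rows) a Wald interval for the difference covers 95.0 to 95.3%.

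**One prognostic factor, two equal halves, 299 per arm, 200,000 simulations.** Excess width is from the formula.

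| Rates (%) | R | Size, chi-squared | Excess width | Power for +10 points, chi-squared → CMH |
|---|---|---|---|---|
| 30 vs 15 | 0.97 | 4.6% | 1.65% | 78.7 → 79.5% |
| 40 vs 15 | 0.92 | 4.2% | 4.2% | 75.3 → 77.6% |
| 50 vs 20 | 0.90 | 4.0% | 5.3% | 71.3 → 74.5% |
| 60 vs 20 | 0.83 | 3.2% | 9.5% | 71.8 → 76.8% |

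The formula gives sizes of 4.6, 4.1, 3.9 and 3.2% for these four cases, within about 0.1 point of the simulation. The stratified test stays at 4.9 to 5.1% throughout.

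**The case against.** The strongest case against the point runs as follows.

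- *The p-values are descriptive.* This stands. Toxicity lies outside the Bonferroni-Holm procedure, and no confirmatory decision or error rate depends on the test. The deviation is also in the safe direction: no inflated false positives and no under-coverage.
- *Nothing shows that the strata predict toxicity.* This stands. Dose and target-volume rules do not differ by Gleason score or indication, and hormonal therapy is an exclusion criterion for all patients. The severe toxicity cited from prospective and cohort data in the Background and Discussion is rare, which is where the effect vanishes. Milder events may be commoner, but no rates by stratum are given.
- *The interval method is not named.* This stands. Excess width is a consequence only if the intervals are unstratified as well.
- *The as-treated safety set need not keep exact balance, and chronic toxicity will have losses.* This weakens the calculated sizes, not the remedy: if treatment switching unbalances the strata, stratifying also guards against that.
- *The SAP may settle it.* It may, since the article defers details to it. But the article names a specific test, so a change has to be made expressly.

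A reader might infer that the toxicity intervals and p-values are materially too conservative, or that toxicity is the one analysis to drop strata used everywhere else. The documents support neither. The larger effects need wide assumed differences between strata. The strata are named only for the primary regression and the Cox models; quality of life and other secondary endpoints have no stated stratification either.

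**Conclusion.** The point holds as a low-severity improvement. The article fixes an unstratified test for a comparative secondary aim in a stratified trial. If Gleason score or indication predicts toxicity, that test and any unstratified interval are slightly conservative: about 4.6 to 4.9% true size, intervals 0.4 to 1.6% too wide and less than one point of power lost under modest gradients. The effect is negligible for rare events. It reaches 3.2 to 4.2% size in the two-group scenarios with rates 25 to 40 points apart (ratios of 2.5 to 3). If the strata are not prognostic, there is no effect.

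These figures rest on assumed stratum rates, equal strata and balance preserved in the analysed set. The planned analysis is valid; it leaves a little precision unused.

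**What to change.** In the Statistical analysis section, or in the SAP before database closure, replace the chi-squared sentence. Report each pairwise toxicity comparison in the safety population as a Mantel-Haenszel risk difference with its 95% CI, with a Cochran-Mantel-Haenszel descriptive p-value over the four randomisation strata. Keep the crude rates by arm beside it. For very rare events, use an unstratified exact method.

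The cost is one sentence. The stratum variables are already recorded for randomisation, so no new data are needed, and essentially nothing is lost if the strata turn out not to be prognostic.
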